### Recruitment

Recruitment will be based on the voluntary demand of women referred to the hospital for contraception from primary care units in the Northern Zone of the city of São Paulo or the Gynecological Emergency Department of the Mandaqui Hospital Complex.

### Collection of patient history and risk factors

The patient history will be collected from all participants using a questionnaire. In addition to general demographic data (age, sex, marital status, occupation, educational level, and income), the medical history will cover chief complaints, current disease status, past medical history, medications in use, smoking, alcohol consumption, the use of systemic antibiotic therapy in the previous 12 months, hospitalization or infection (including skin infections) in the previous 12 months, previous IUD use, and preferred contraceptive methods. This questionnaire will enable the correlation of clinical, demographic, and epidemiological risk factors with the study outcomes in this population.

### Allocation (Sequence generation, allocation concealment mechanism, implementation)

A random sequence generator available online (https://www.sealedenvelope.com/) will be used to select the block randomization option with two treatments at a 1:1 ratio, resulting in equal numbers of patients in each group (n = 36 per group). As the total sample size is 72 patients, 12 blocks of six patients each will be established. Opaque envelopes will be sequentially numbered (1–72) and will contain the randomized group allocation. These envelopes will be sealed and stored securely until the IUD is placed. Only the designated researcher responsible for treatment will be aware of the assigned intervention. After opening, the envelope will be resealed and stored with the patient’s medical record, remaining concealed until the final statistical analysis. An individual not directly involved in the study will generate the random sequence and prepare the envelopes.

All participants will undergo the same IUD placement protocol performed by the same healthcare provider, as described in the “IUD Placement Protocol” section. Immediately after placement, the researcher in charge of applying PBM will retrieve and open an envelope, maintain the order of the remaining envelopes, and administer the assigned treatment (active or sham PBM). Only this researcher will be aware of the allocation.

The main investigator will oversee data storage (digital platforms) and organization. The statistician will be responsible for data analysis and will remain blinded to the interventions. The envelopes will also store participant records (patient history questionnaire, demographic data, risk factors, and statement of informed consent) and will be securely archived.

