### Blinding (Masking)

Only the researcher in charge of administering the treatment (who opens the randomization envelopes) will be aware of the assigned intervention for each participant. The participants will be blinded because of the visual similarity of the treatments (LED on versus LED off). The researcher collecting the outcome data will also be blinded to the interventions and will not be present in the room during treatment. Group allocation will be disclosed only after the statistical analysis is completed, ensuring that the data collector and statistician remain blinded. Unblinding during the trial is not planned, as no adverse events are expected with PBM use.

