### Ethical aspects

This study ensures compliance with applicable ethical and regulatory guidelines. No modifications to the research protocol are planned; however, if any arise, they will be promptly communicated to all relevant parties, including investigators, the ethics committee (via an amendment submission), participants, and clinical trial registries. A trained researcher will obtain informed consent after providing the participants with detailed information about the objectives, procedures, risks, and benefits of the study, using a consent form written in clear, accessible language. No biological materials will be collected or stored. The collection, sharing, and storage of the participants’ personal information will follow strict data protection protocols to ensure confidentiality before, during, and after the trial. All data will be anonymized and securely stored to prevent unauthorized access. There are no financial or other conflicts of interest. Only the main investigator will have access to the final dataset. The researcher in charge is committed to disseminating the survey results to the participants, healthcare professionals, and the public through publications and presentations at conferences while respecting any previously agreed-upon publication restrictions.

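### Constant, published blocks of six let the researcher who opens the envelopes deduce about a quarter of assignments in advance; biased enrolment follows only if that person has a hand in enrolment

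*Protocol article*

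**What the plan says.** All of the allocation rules are in the protocol article.

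- **Block structure (Allocation).** "As the total sample size is 72 patients, 12 blocks of six patients each will be established", with "two treatments at a 1:1 ratio, resulting in equal numbers of patients in each group (n = 36 per group"). Each block therefore holds three active and three sham assignments. The trial is single-centre (Materials and methods) and no stratification is stated, so there is one list.
- **Concealment (Allocation).** "Opaque envelopes will be sequentially numbered (1–72) and will contain the randomized group allocation". They are sealed, and "An individual not directly involved in the study will generate the random sequence and prepare the envelopes".
- **Who opens them (Allocation).** "Immediately after placement, the researcher in charge of applying PBM will retrieve and open an envelope, maintain the order of the remaining envelopes".
- **Who knows the result (Blinding).** "Only the researcher in charge of administering the treatment (who opens the randomization envelopes) will be aware of the assigned intervention for each participant".
- **Who enrols.** Materials and methods has the main investigator explain the study before women sign the consent form. Calibration/Training has the same person perform all placements. Ethical aspects says: "A trained researcher will obtain informed consent after providing the participants with detailed information", without saying which researcher this is.
- **Timing.** Materials and methods gives the status as not yet recruiting, with an anticipated start of March 30, 2026.

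**The concern.** To predict the next assignment in a blocked list, a person needs the block size and the assignments already made in the current block. The article prints the first. Its procedure gives the second, complete and in order, to one researcher. An opaque sealed envelope hides its own contents but cannot prevent deduction from the envelopes before it. Opening the envelope late does not help either, because a forced assignment is known before the woman is approached.

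What is at stake is allocation concealment in a trial with a self-reported pain outcome. If someone who can foresee the next arm also influences who is enrolled, or when, the arms can differ at baseline for reasons other than chance. No analysis reliably repairs that afterwards.

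**Working it through.** **Inputs (Allocation section).** 12 blocks, block size 6, ratio 1:1, 72 envelopes, 36 per group.

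**The plan's own figure.** 12 × 6 = 72 and 72 / 2 = 36. It reproduces, so every block must contain 3 + 3.

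**Assignments known with certainty.** An assignment is forced once one arm has used its three places in the block. There are C(6,3) = 20 equally likely orders:

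- 12 orders have 1 forced assignment
- 6 orders have 2
- 2 orders have 3

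Mean = (12×1 + 6×2 + 2×3) / 20 = 30/20 = 1.5 per block. The closed form 2h/(h+1) with h = 3 gives 6/4 = 1.5 as well. As a share this is 1.5/6 = 25%. Over 12 blocks it is 12 × 1.5 = 18 of 72.

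The variance per block is (12×1 + 6×4 + 2×9)/20 − 1.5² = 2.70 − 2.25 = 0.45, so the SD over 12 blocks is √(12 × 0.45) = 2.3. The central 95% range is about 14 to 23. The minimum is 12, because the sixth place is always forced.

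**By place in the block, for an observer who knows the history:**

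| Place | Certain | Best guess correct |
|---|---|---|
| 1 | 0% | 0.5 |
| 2 | 0% | 3/5 = 0.6 |
| 3 | 0% | (2/5)(3/4) + (3/5)(1/2) = 0.6 |
| 4 | 2/20 = 10% | 0.1×1 + 0.9×(2/3) = 0.7 |
| 5 | 8/20 = 40% | 0.4×1 + 0.6×0.5 = 0.7 |
| 6 | 100% | 1.0 |

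The certain shares sum to 1.5. The best-guess column sums to 4.1 of 6, or 68.3%, against 50% with no information.

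**Effect of varying the block size.** This was simulated with 2,000 lists of 72. Sizes were drawn at random with equal probability, and the observer was assumed to know the set of possible sizes but not which was used when.

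| Block sizes | Certain | Best guess correct |
|---|---|---|
| 6 only | 25.0% | 68.3% |
| 4, 6 | 5.6% | 69.1% |
| 2, 4, 6 | 4.2% | 70.0% |
| 4, 6, 8 | 2.2% | 67.8% |

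With sizes 4, 6 and 8, about 0.022 × 72 = 1.6 assignments remain certain instead of 18. Best-guess accuracy hardly moves.

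**The case against.** The strongest reply is that the person who can predict is not shown to be a person who enrols. The main investigator explains the study and places the device. Only the PBM researcher knows past allocations, and a printed block size is useless without that history. The PBM researcher's described task is to open the envelope and apply active or sham treatment. Women arrive by referral, an independent person prepares the list, and the envelopes are numbered, opaque and sealed. Staffing detail is also something an article may leave to the full protocol.

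Most of this stands. A reader might infer that a quarter of allocations will be known to whoever recruits, or that selective enrolment is built in. The documents support neither. They give the PBM researcher no role in consent, eligibility or scheduling, and they describe no disclosure to the main investigator. Opened envelopes are resealed and kept with the medical record, and the main investigator oversees data storage. That is a conceivable leak, but the text says the contents stay concealed until the final analysis. The absence of a fuller list of roles is not itself the criticism.

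Two things remain. The constant block size is a stated and published rule, not an omitted detail. And consent is obtained by an unidentified trained researcher, which does not exclude the PBM researcher.

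The reply is also right that varying the blocks does not lower best-guess accuracy, so that change alone would not end predictability.

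**Conclusion.** The point holds as a cheap improvement to a stated rule, not as evidence of bias. With constant blocks of six and a complete history, the PBM researcher can know 18 of 72 assignments (25%) on average before the woman is allocated, and never fewer than 12. That figure is exact combinatorics and rests only on the block structure, the 1:1 ratio, and one person seeing every allocation in order.

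Harm to the comparison needs a further condition that the documents neither state nor exclude: that this researcher takes part in, or informs, consent, eligibility or scheduling. Its size cannot be estimated from the documents.

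The Allocation section has the envelope opened after placement, while the article describes the treatment as preventive and measures pain during insertion. Those statements must be reconciled, but the 25% is the same either way.

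**What to change.** 1. In the Allocation section, replace the 12 blocks of six with randomly permuted blocks of varying size, for example 4, 6 and 8. The independent person already named generates the list and withholds the block sizes from all study staff until the trial ends. On the simulation's assumptions, certain assignments fall from 25% to about 2% even if the set of sizes becomes known.
2. Add one sentence that the PBM researcher takes no part in consent, eligibility or scheduling, in line with the roles already described. This deals with the best-guess accuracy of about 68%, which step 1 leaves in place.

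**Cost.** If the list is not yet in use, this is one setting when it is generated and a short amendment. The split may depart slightly from 36/36. At worst, 68 women fill complete blocks (34 + 34) and the last four, all in one arm, come from an unfinished block of eight, giving 38/34. Choosing block sizes that total 72 avoids this. The last assignment would then again be known to anyone who has counted the arms and knows that the totals are 36 each, which is a small price.

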**Methods and analysis:**

The proposed randomized, double-blind clinical trial will investigate the effectiveness of PBM at reducing pain during the placement of the copper T 380 IUD. Seventy-two women will be randomly allocated to either an active PBM group (n = 36) or sham PBM control group (n = 36). In all participants, the standard IUD placement protocol will follow the guidelines of the Brazilian Ministry of Health. Pain will be assessed using the Visual Analog Scale (VAS) at multiple time points: during each step of insertion (Pozzi clamp, hysterometry, IUD placement) as well as 5 min, 15 min, 24 hours, and 48 hours post-procedure. The secondary outcomes will be analgesic use, anxiety levels (GAD-7), quality of life (WHOQOL-100), satisfaction with the procedure, and adverse effects. Ethics and dissemination. This clinical trial received approval from the Research Ethics Committee of the Mandaqui Hospital Complex (process: 7.367.867) and was registered in ClinicalTrials.gov (NCT06984796). Statistical analyses will be conducted using SPSS v24.0, with a significance level of 5%. Either parametric or nonparametric tests will be applied, depending on the data distribution. Kaplan-Meier curves will be used to assess time to pain resolution. The results will be disseminated through peer-reviewed publications.

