Given the lack of effective pharmacological interventions, alternative approaches have been explored. Paravertebral blockade between T10 and S4 has shown promise for analgesia during labor [2,5,9], while transcutaneous electrical nerve stimulation (TENS) has been effective at controlling pelvic pain [10,11]. Photobiomodulation (PBM) has demonstrated analgesic effects for lower back pain [12,13] and labor pain [9], suggesting the potential to reduce discomfort during IUD placement [14]. As the Brazilian Ministry of Health does not currently recommend analgesic measures for IUD placement, further studies are needed to assess the effectiveness of PBM at improving patient comfort and increasing adherence to this contraceptive method, ultimately benefiting public health [4]. Our experimental hypothesis is that the use of PBM can reduce pain perception during the placement of the T 380 copper IUD for contraception.

Therefore, the aim of this study is to propose a protocol for the assessment of whether preventive photobiomodulation (PBM) alters pain perception during the placement of the T 380 copper intrauterine device (IUD) for contraception in women without comorbidities.

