**Fig 1 pone.0349031.g001:**
[figure not shown]
Template illustrating recommended content for schedule of enrollment, interventions, and assessments.

The study protocol (original language S2 File; in English S3 File) received approval from the Research Ethics Committee of the Mandaqui Hospital Complex in São Paulo, Brazil (7.367.867). The original document (S4 File) and a translation (S5 File) were presented Any unforeseen events or modifications during the study will be reported to the ethics committee and disclosed in future publications. After the main investigator provides a verbal and written explanation of the study, individuals who agree to participate will sign an informed consent form. Participants who wish to receive the study results will provide their email addresses and the full article will be shared upon publication. The participants will be involved in the development of the study design and the execution of the trial but not involved in the data analysis or reporting.

Treatment will be performed at the Mandaqui Hospital Complex in the northern region of São Paulo, Brazil. The main investigator is a gynecologist with more than 10 years of experience and will perform the procedures. According to the ClinicalTrials.gov record (NCT06984796) (S6 File), the study is currently listed as “Not yet recruiting”, with an anticipated starting date of March 30, 2026, and a primary completion date of May 30, 2027. The study was registered in ClinicalTrials.gov (NCT 06984796) and is in accordance with the SPIRIT 2025 Guidelines Checklist Statement.

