### Calibration/Training

A single examiner will assess five women who will not be included in the study. These women will undergo clinical pain assessments identical to those proposed for the trial.

The main investigator will perform all IUD placement procedures and postprocedural assessment. This investigator will also undergo specific training for the following outcomes: anxiety, using the Generalized Anxiety Disorder 7 (GAD-7) questionnaire; quality of life, using the WHOQOL-Pain instrument; and patient satisfaction, using a questionnaire based on the method proposed by Lopes *et al.* (2015) [6].

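### The allocation section has PBM given after the IUD is placed, so the insertion pain scores that the trial sets out to reduce would precede treatment

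*Protocol article*

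**What the plan says.** **Timing of treatment.** The section Allocation gives the timing in two places. On storage of the envelopes: "These envelopes will be sealed and stored securely until the IUD is placed". On the action itself, after stating that all participants undergo the same placement protocol: "Immediately after placement, the researcher in charge of applying PBM will retrieve and open an envelope". That researcher then gives the assigned active or sham PBM.

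**Purpose.** According to the abstract (Methods and analysis), the trial "will investigate the effectiveness of PBM at reducing pain during the placement of the copper T 380 IUD". The Introduction's hypothesis is that "the use of PBM can reduce pain perception during the placement of the T 380 copper IUD for contraception", and its aim is to assess "whether preventive photobiomodulation (PBM) alters pain perception during the placement of the T 380 copper intrauterine device". The title of Table 1 and the legend of Fig 3 also call the irradiation preventive. The legend places it during IUD placement, which is a third version of the timing.

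**Primary outcome.** Pain on the VAS is recorded at eight times: baseline, Pozzi clamping, hysterometry, IUD placement, 5 minutes, 15 minutes, 24 hours and 48 hours.

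**Who is in the room.** Under Calibration/Training: "The main investigator will perform all IUD placement procedures and postprocedural assessment". Under Blinding (Masking): "The researcher collecting the outcome data will also be blinded to the interventions and will not be present in the room during treatment".

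**The concern.** A treatment given after the device is in place cannot reduce pain felt while it was being placed. Followed literally, the allocation section puts the three scores closest to the trial's question before both the envelope and the irradiation. The trial could then say something about pain after placement, but nothing about its own hypothesis.

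If the wording is only a slip, it still stands as a written instruction to the person who opens the envelope and treats. Nothing elsewhere in the article's text overrides it: the IUD placement protocol contains no PBM step, and Group composition gives the position and dose of the irradiation but not its timing relative to insertion. Insertion scores collected before treatment cannot be recovered once participants have been through the procedure.

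**Working it through.** The check is one of time order. It uses no power or error-rate calculation.

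**Step 1: count the scores that PBM could affect.** The eight times come from the section Primary outcome. Order A is the allocation section as written. Order B has PBM completed before the Pozzi step.

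| VAS score | Order A: PBM after placement | Order B: PBM before Pozzi |
|---|---|---|
| Baseline | before treatment | before treatment |
| Pozzi | before treatment | can respond |
| Hysterometry | before treatment | can respond |
| IUD placement | before treatment | can respond |
| 5 min | can respond | can respond |
| 15 min | can respond | can respond |
| 24 h | can respond | can respond |
| 48 h | can respond | can respond |

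- Insertion scores taken before treatment under order A: 3/8 = 37.5%.
- Scores able to respond under order A: 4/8 = 50%.
- Scores able to respond under order B: 7/8 = 87.5%.

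Under order A the arms have been handled identically up to and including the third insertion score, and nobody treating or assessing knows the allocation. The expected difference between arms at those three times is therefore zero, whatever PBM does.

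**Step 2: the 5-minute and 15-minute scores under order A.** Table 1 gives an irradiation time of 20 min and an application time of 10 min. Its dose rows agree with 10 min:

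- Energy per LED: 8 mW × 600 s = 4.8 J, as tabulated. At 1200 s it would be 9.6 J.
- Radiant exposure: 16 mW/cm² × 600 s = 9.6 J/cm², as tabulated. At 1200 s it would be 19.2 J/cm².

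Assume irradiation starts *s* minutes after placement, with 0 ≤ *s* < 5. The article says only that it follows immediately, so this range is an assumption.

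- Duration 10 min: irradiation ends at *s* + 10, that is from 10 to just under 15 min. The 5-minute score falls inside the irradiation and the 15-minute score outside it, so 1 of the 4 responsive scores is taken during treatment.
- Duration 20 min: irradiation ends at *s* + 20, that is from 20 to just under 25 min. Both scores fall inside, so 2 of the 4 are taken during treatment.

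**Step 3: blinding at the 5-minute score.** Under either duration, somebody must collect the 5-minute score while the panel is in place, switched on or off. The Blinding section keeps the outcome collector out of the room during treatment. The training section gives postprocedural assessment to the main investigator. Under order A these arrangements clash at that score.

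**The case against.** The strongest reply is that the sources which normally fix the sequence are not to hand. Fig 1 (schedule), Fig 2 (flowchart) and the full protocol in the supplementary files may show PBM in the right place. That is possible, and it would make a drafting error more likely. It would not cure the allocation section, which would then contradict those sources as well as the aim. The point is about something stated wrongly, not something left out.

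A second reply runs the other way: treatment after placement may be intended. The timing appears twice in the allocation section. One secondary outcome is the time to relief of abdominal discomfort following PBM, counted from the onset of cramps. The patient also lies down for about 15 minutes after placement, long enough for a 10-minute irradiation. These points are fair, and for that reason the investigators must say which order they mean. If it is the later one, the aim, hypothesis and preventive label are what is wrong.

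Three smaller points stand in part:

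- The IUD placement section describes standard ministry practice for both arms, so the absence of a PBM step there does not confirm the allocation text. It only fails to correct it.
- No sentence says outright that the main investigator collects the 5-minute VAS. The clash with the blinding section nevertheless applies to whoever does.
- The percentages count time points with equal weight. They do not measure lost power or bias.

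**Conclusion.** The concern holds. The allocation section contradicts the aim, the hypothesis and the preventive label, and no other text in the article resolves the contradiction.

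Conditional on the allocation section being followed, all three insertion scores (3 of 8) precede treatment, the number of scores able to respond falls from 7 to 4 of 8, and the hypothesis about pain during placement cannot be tested. This rests on time order alone. The further finding, that one responsive score (10-minute irradiation) or two (20-minute) fall during treatment, assumes a start within 5 minutes of placement.

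Whether the wording is a slip or the true plan cannot be settled from the article. A correction is needed in either case, before the first participant is enrolled.

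**What to change.** **If PBM is meant to precede insertion**, which the aim and the preventive label suggest:

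- Correct both timing sentences in the allocation section so that the order is baseline VAS, envelope opened, active or sham PBM completed, then the Pozzi step.
- State that the main investigator is out of the room during irradiation, and add the PBM step to the IUD placement protocol.
- Change the Fig 3 legend from irradiation during placement to irradiation before it. The main investigator inserts the device and makes the postprocedural assessment, so irradiation during insertion would put that assessor beside a panel that is visibly on or off.

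**If PBM is meant to follow insertion:**

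- Restate the abstract objective, aim, hypothesis and primary outcome as post-placement pain, and remove the word preventive from the Introduction, Table 1 and Fig 3.
- Treat the baseline and three insertion scores as pre-treatment covariates.
- Settle who collects the 5-minute score and how that person stays blinded, or move the score to after irradiation ends.

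**Cost.** This is a wording correction through the amendment route already described under Ethical aspects (ethics committee and registry). The article lists the trial as not yet recruiting, "with an anticipated starting date of March 30, 2026". No extra participants or procedures are needed: either the same irradiation is moved or the aim is restated.

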### IUD placement protocol according to the recommendations of the ministry of health

Before the procedure, the steps will be explained to the patient again to reduce anxiety and promote relaxation during IUD placement. A two-hand pelvic examination will be performed to assess the size, position, and mobility of the uterus. Infection prevention measures will be implemented, including the use of sterile gloves and cervical cleansing with a chlorhexidine-based antiseptic. The anterior lip of the cervix will be gently grasped with Pozzi forceps to ensure stabilization during placement. A hysterometer will be introduced slowly and carefully to determine uterine depth and angulation, thus minimizing the risk of perforation. During IUD preparation, all instruments and gloves will be maintained sterile, and the device will be assembled according to the manufacturer’s instructions, with the arms kept horizontal during insertion. The retractable technique will be used for placement. The insertion tube will be advanced to the uterine fundus. The tube will then be partially withdrawn while keeping the plunger fixed, thereby releasing the arms of the IUD. After a few seconds, the plunger and insertion tube will be removed. The IUD strings will be trimmed to 2–3 cm from the cervix. The patient will remain lying down for approximately 15 minutes to reduce discomfort. Following placement, the patient will be monitored for well-being and possible vasovagal reactions (e.g., sweating, nausea, or fainting), which are rare and self-limiting. The length of the IUD strings relative to the cervix will be documented in the medical record. The patient will be instructed to return for a follow-up visit in 30 days to verify IUD positioning and adaptation.

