### Data management and quality control

All data will be collected using standardized forms and recorded by trained researchers. The data will be entered into a secure electronic database and checked for completeness and consistency. Periodic data verification will be performed to identify inconsistencies or missing values, which will be reviewed and corrected against the original records. Access to the database will be restricted to authorized members of the research team. All data will be anonymized prior to analysis to ensure participant confidentiality.

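### One resealed envelope holds both the arm and baseline source forms, so checking those forms before analysis may show the arm to staff meant to stay blinded

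*Protocol article*

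**What the plan says.** The Allocation section of the protocol article describes 72 numbered opaque envelopes that carry the assignment. On what happens after one is opened, it says: "After opening, the envelope will be resealed and stored with the patient’s medical record, remaining concealed until the final statistical analysis". On who may know the arm, it says of the researcher who applies PBM: "Only this researcher will be aware of the allocation". The same section gives the envelopes a second use: "The envelopes will also store participant records (patient history questionnaire, demographic data, risk factors, and statement of informed consent) and will be securely archived".

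Four other statements bear on this:

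- The Blinding (Masking) section keeps the outcome collector and the statistician blinded, and allows disclosure only once the analysis is finished.
- The Data management and quality control section provides for periodic verification of inconsistent or missing values, "which will be reviewed and corrected against the original records".
- The section on patient history and risk factors plans to relate the questionnaire data to the study outcomes, so these forms feed the analysis.
- The Calibration/Training section says: "The main investigator will perform all IUD placement procedures and postprocedural assessment".

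**The concern.** The envelope is given two jobs that pull against each other. As the carrier of the allocation, it has to stay shut until the analysis. As the store for baseline and consent forms, it has to be accessible whenever one of those forms is queried, and queries come before the analysis.

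What is at stake is the blinding of two parties. The first is whoever enters and verifies the data. The second is the main investigator, who assesses participants after the procedure and is not among those allowed to know the arm. The primary outcome is a self-reported pain score, and adverse effects are elicited by an open question followed by prompts. With outcomes of this kind, an assessor's knowledge of the arm can influence how questions are put and how answers are recorded.

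**Working it through.** No arithmetic applies. The check sets the statements side by side.

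1. **Contents.** By the Allocation section, the numbered envelopes hold the assignment. By the same section, the envelopes also hold the background questionnaire, demographic and risk-factor data, and the signed consent. No other kind of envelope is introduced, so the natural reading is one envelope per participant holding both.
2. **Access rule.** The envelope is resealed and stays concealed until the final analysis. Only the PBM researcher may know what it shows.
3. **Need for access.** The Data management section calls for corrections against original records. The questionnaire data are to be related to outcomes, so they are study data and are covered by that requirement. If the forms in the envelope are the originals, a query on a baseline value before the analysis leads back to the envelope.
4. **Conflict.** When such a query arises, there are three possibilities: the check is not made, the PBM researcher retrieves the form, or someone else opens the envelope and can see the arm. The article does not choose between them. It mentions no inner sealed slip and no separate filing, and it names nobody who may reopen an envelope.
5. **Early data entry does not settle it.** Forms could be entered before they are filed. Correction against the originals comes after entry, so the need to return to them remains.
6. **Which outcomes could be touched.** On the Allocation section's own timing, the envelope is opened immediately after placement. The three insertion-phase pain readings are then already taken and cannot be affected. Later assessments could be affected only if the assessor had seen the arm by then.

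**The case against.** The best case for the plan has five parts.

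- **Nothing prescribes opening by blinded staff.** Followed literally, the envelope is resealed and stays shut. The Data management section names no verifier, and the unblinded PBM researcher could fetch a form. This stands. A reader might infer that blinded staff must reopen envelopes in routine work, but the documents do not say so.
- **Only baseline and consent forms are listed.** No pain-scale, anxiety, quality-of-life, tablet-count or adverse-effect form is among the contents. This stands. Verifying an outcome value does not lead to the envelope, and correcting a demographic entry does not change a pain score.
- **The later readings cannot be counted as exposed.** A reader might infer that two of the seven post-baseline pain readings (24 and 48 hours) come after filing and are compromised. The article does not say when the resealed envelope is filed, and these readings are ratings by participants who are themselves meant to be blinded. That count would be an assumption.
- **The link to the main investigator's working file is thin.** The article says "The length of the IUD strings relative to the cervix will be documented in the medical record", but it does not say who writes this entry. The entry concerns the placement itself, so it does not show the record in use after the envelope is filed with it. The statement "The main investigator will oversee data storage (digital platforms) and organization" refers to digital platforms and does not establish custody of paper envelopes. This stands too.
- **Custody details belong in the full protocol.** This is a fair point about matters the article leaves out. It does not answer a filing rule that the article states, which is the shared envelope.

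What survives is the conflict between keeping the envelope concealed and keeping source forms inside it.

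**Conclusion.** The point holds as an avoidable weakness in the protection of blinding. Allocation and original baseline forms share one envelope, kept with the medical record. A check of those forms before the analysis may require opening an envelope that shows the arm, and the article gives no route for the check that keeps blinded staff away from it.

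The size can be stated only as a range. The rule covers all 72 envelopes, and the number opened before the analysis could be anywhere from none to all of them. No effect on the treatment comparison can be calculated from the documents.

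The conclusion rests on two assumptions: that the forms in the envelope are the original records meant in the Data management section, and that no inner seal separates the assignment from the forms. The article states neither explicitly. The stronger reading, that the plan itself unblinds the assessor or the data handlers, is not supported. The risk is left open by the plan, and unblinding is not a prescribed step.

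**What to change.** Replace the shared-envelope rule in the Allocation section with two statements:

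- The opened allocation slips are filed apart from the medical record and from all participant forms. They are held by the PBM researcher or by the independent person who prepared the sequence, until the analysis is complete, as the Blinding section already requires.
- The history, demographic, risk-factor and consent forms are kept in a participant file with no allocation information, and only that file is used for data entry and verification.

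The cost is two sentences and one separate file to maintain, with no extra staff. The article reports the trial as not yet recruiting. If that is still so, the change can be made before any envelope is opened.
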